**Table 5: Recommended Changes in Therapy**

| Imaging                                                                        | Recommended treatment                                                                                     |                                                                                               |
|--------------------------------------------------------------------------------|-----------------------------------------------------------------------------------------------------------|-----------------------------------------------------------------------------------------------|
| Disease in Para-aortic nodes                                                   | EFRT                                                                                                      | Extend radiation field to include Para-aortic nodes to T12/L1                                 |
| Disease identified in pelvic nodes or presacral nodes                          |                                                                                                           | Extend superior pelvic margin to include common iliac nodes to L4 and/or include whole sacrum |
| Disease identified in common iliac nodes                                       |                                                                                                           | Extend superior pelvic field margin to include low Para-aortic nodes i.e., L1/2               |
| Extensive disease identified in primary cervix tumor or pelvic nodes           | Modify pelvic radiation fields without EFRT                                                               |                                                                                               |
| More extensive cervical disease e.g. uterine extension                         | Change brachytherapy volume or dose                                                                       |                                                                                               |
| Supraclavicular nodes, mediastinal nodes, bony mets, other solid organ disease | Palliative care only ie., chemo alone or palliative radiation therapy, clinical trials or supportive care |                                                                                               |

## **1.7. Work of Investigators**

The Ontario Clinical Oncology Group (OCOG) has led the field evaluation program for PET in oncology in Ontario. OCOG has worked with a network of investigators to design, implement and conduct six clinical trials evaluating  $^{18}\text{F}$ FDG PET for the following clinical indications; staging of early lung cancer patients being considered for surgery, staging of patients with locally advanced lung cancer and using  $^{18}\text{F}$ FDG PET to plan radiation, detection of neck metastases post-radiation in head & neck cancer, staging of the axilla in women with early breast cancer who undergo sentinel node biopsy, staging of colorectal cancer metastatic to the liver prior to surgery, and diagnosing recurrence of tumour in situations where conventional imaging has been inconclusive. To-date, 1800 patients have been entered in these trials.

Three of these studies are randomized trials and three are prospective cohort studies. Three have been completed and presented at international meetings. As part of the evaluation project, OCOG organized a quality assurance process that included: reading of PET scans by nuclear medicine physicians, standardizing the dose of FDG used for PET imaging across the province, and calibration of the five PET scanners to the same standards.

The dedicated group of radiation, medical and gynecologic oncologists participating in this study has extensive experience in enrolling patients into cervical cancer trials through co-operative trials groups. In addition, there is an experienced team of radiation oncologists, radiologists and nuclear medicine physicians who have participated in the six OCOG PET studies.

## **1.8. Study Rationale**

This is an opportune time to perform a trial in locally advanced cervical cancer because there is considerable debate worldwide regarding the utility of PET for staging cervical cancer. Although there are studies on the accuracy (sensitivity and specificity) of PET in cervical cancer, there is only one small prospective randomized study on how PET information affects treatment decisions and outcomes. As a result, PET may be underutilized for staging cervix cancer.

The costs associated with health care are increasing and PET is an expensive imaging modality. Given that resources for health care are not unlimited, there needs to be high quality evidence of an intervention such as PET's efficacy. To this end, the Ministry of Health and Long Term Care (MOHLTC) has been sponsoring a field evaluation consisting of clinical trials to generate the evidence. There are a core number of PET-CT units available in Ontario, and because of past work in PET and oncology, the clinical protocols are standardized. With the effort of OCOG and the Ontario MOHLTC, there is a system in place to complete this work.

## **2. STUDY OBJECTIVES**

### **2.1. General Objective**

To improve the clinical management and outcome of patients with locally advanced cervical cancer by using FDG PET-CT imaging.

### **2.2. Primary Objective**

In women with FIGO Stages IB-IVA carcinoma of the cervix who are candidates for chemo-RT, to compare the treatments delivered between patients having whole body FDG PET-CT in addition to CT of the abdomen and pelvis versus patients having a CT of the abdomen and pelvis alone. The treatment delivered will be classified as standard pelvic chemo-radiotherapy of curative intent; more extensive chemo-radiotherapy of curative intent such as EFRT; or therapy with palliative or non-curative intent (i.e. which may include symptom management, radiation, chemotherapy or combined modality therapy, used to maximize disease and symptom control).

### **2.3. Secondary Objectives**

In women with FIGO Stages IB-IVA carcinoma of the cervix who are candidates for chemo-RT:

1. To compare the event-free survival (EFS) of patients who undergo pre-treatment imaging using FDG PET-CT in addition to CT of the abdomen and pelvis with the EFS of patients who undergo pre-treatment CT of the abdomen and pelvis alone.
2. To compare the overall survival (OS) of patients who undergo pre-treatment imaging using FDG PET-CT in addition to CT of the abdomen and pelvis with the OS of patients who undergo pre-treatment CT of the abdomen and pelvis alone.
3. To investigate whether the PET standardized uptake value (SUV) of cervical cancer is prognostic for EFS and OS.
4. To conduct economic and quality of life (QoL) analyses of the strategy of pre-treatment imaging using FDG PET-CT in addition to CT of the abdomen and pelvis compared with a strategy of pre-treatment CT of the abdomen and pelvis alone.

## **3. STUDY DESIGN**

A multicentre randomized controlled trial to determine the impact of pre-treatment staging with whole-body FDG PET-CT in addition to CT of the abdomen and pelvis compared to CT of the abdomen and pelvis alone in patients with potentially curable cervical cancer being assessed for chemo-RT. (Refer to Study Schema).

After initial assessment, eligible consenting patients will be randomized to either pre-treatment whole-body FDG PET-CT in addition to CT of the abdomen and pelvis or CT of the abdomen and pelvis alone. Patients with disease confined to the pelvis will be treated with standard chemo-RT. If there is suspicion of metastatic disease, investigators will be encouraged to perform additional investigations to confirm the presence of the disease histologically, if possible (although this is not mandatory). If investigation or biopsy of

suspicious lesion(s) is inconclusive or not performed, the patient will receive treatment at the discretion of the radiation oncologist. If the patient has metastatic disease outside of potentially radiated areas, she will be offered palliative therapy either by chemotherapy alone, or palliative RT or symptomatic management. The primary outcome is treatment delivered to the patient. Patients will be followed for approximately 5 years.

## **4. STUDY POPULATION**

### **4.1. Screening for Potentially Eligible Patients**

Written informed consent will be obtained from all potentially eligible patients prior to commencing any study related screening or treatment procedures. Until the patient has been completely informed of the clinical trial, has freely consented to take part in the study and has signed and dated an informed consent form that has received documented approval by a licensed Research Ethics Board (REB), no study related procedures, including those required for screening can be performed.

### **4.2. Eligibility Criteria**

Eligibility status must be confirmed by the local investigator prior to randomization. It is important that no exceptions be made to the eligibility criteria. Questions related to eligibility requirements and/or specific criteria must be discussed with OCOG prior to randomization.

#### **4.2.1. Inclusion Criteria**

For inclusion in this study, patients must fulfill all of the following criteria:

1. Women with newly diagnosed histologically confirmed FIGO Stage IB-IVA carcinoma of the cervix (see **Appendix I**), including squamous, adenosquamous or adenocarcinoma. Women not suitable for surgery due to comorbidities (medical or other conditions) are also considered eligible;
2.  $\geq 18$  years of age;
3. Being considered for treatment with curative intent using concurrent chemotherapy and pelvic RT.

#### **4.2.2. Exclusion Criteria**

Patients who satisfy any of the following exclusion criteria are NOT eligible for this study. These criteria will apply only to those patients who first satisfy the inclusion criteria:

1. ECOG performance status  $> 2$  (see **Appendix II**)
2. Other cervical cancer tumour types (e.g. neuroendocrine, serous)
3. Carcinoma of the cervical stump
4. Prior hysterectomy
5. Patients who, at the time of the initial evaluation, have already undergone a whole body PET-CT within the last 6 months

6. Contraindications to  $^{18}\text{F}$ FDG PET-CT
7. Inability to lie supine for imaging with PET-CT
8. Contraindication to radiotherapy (i.e., significant Crohn's disease)
9. Contraindication to cisplatin chemotherapy (i.e., non-reversible renal failure)
10. Inadequate bone marrow function: ANC  $<1.5 \times 10^9$ , platelets  $<100 \times 10^9$
11. Inadequate renal function: Creatinine  $\geq 150$  micromol/L
12. Inadequate hepatic function: Bilirubin  $>1.5 \times \text{ULN}$  and SGOT and Alkaline Phosphatase  $>3 \times \text{ULN}$
13. History of another invasive malignancy within the previous 5 years with the exception of non-melanoma skin cancer
14. Other medical conditions that may preclude chemo-radiation therapy
15. Known pregnancy or lactating
16. Inability to complete the study or required follow-up.

## 5. PRE-TREATMENT EVALUATION

### *Refer to Appendix III: Schedule of Study Assessments and Evaluations*

The Baseline assessment is to include documentation of cancer staging as per FIGO staging criteria (see **Appendix I**). The presence of relevant comorbidities and ECOG performance status is to be recorded. Physical exam will include the assessment of height and weight.

Other baseline assessments will include: a chest X-ray (or chest CT scan) and blood tests (creatinine and random blood sugar) within a 28 day period prior to randomization. Pelvic MRI as performed according to local centre practice will be documented and utilized for stratification at the time of randomization. Patients may or may not have had a contrast-enhanced CT scan of the abdomen and pelvis at the time of randomization. If a patient has had a contrast-enhanced CT scan of the abdomen and pelvis it must have been done within 6 weeks of randomization. Otherwise, the CT scan needs to be repeated (see **Section 7.2** for minimum standards and **Appendix VI, item 6.** for contrast-enhanced CT scan procedures).

The QoL questionnaires (EORTC QLQ-30 version 3 and EORTC QLQ-CX24, see **Appendix IV**) and the questionnaire to measure health utilities (EQ-5D, see **Appendix V**) are to be completed by the patient after informed consent has been obtained. It is preferable for the patient to complete these questionnaires prior to randomization, although this is not mandatory.

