### **13.3. Analysis Sets**

All patients who are randomized will be included in the Full Analysis set. All patients who complete the baseline QoL and at least one follow-up QoL questionnaire will be included in the QoL Analysis set.

Analysis of the treatment delivered, EFS and OS will be based on the Full Analysis set with patients included in groups according to their randomized allocation (i.e. intention-to-treat principle). A secondary analysis of treatment delivered, EFS and OS will be performed on the protocol evaluable analysis set, defined as the subset of patients in the Full Analysis set excluding patients with disease which has spread to distant organs. Analysis of QoL and economic outcomes will be based on the QoL Analysis set. Investigation of the prognostic ability of PET SUVs will be based on the patients who underwent PET-CT.

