### **13.4. Health Related Quality of Life Data**

Overall QoL will be assessed using the EORTC QLQ-C30 version 3, and disease-specific QoL using the EORTC QLQ-CX24. The mean and standard deviation of each QoL domain will be calculated at each time point, along with changes from baseline. The profile of the QoL scores will be plotted and compared between the two arms. A repeated measures regression model with an unstructured covariance structure will be used to evaluate the effect of the intervention longitudinally. Other covariance structures may be used if necessary. Descriptive statistics, plots and tables will also be used to explore for an effect on QoL between CT of the abdomen and pelvis + PET-CT and CT of the abdomen and pelvis alone over time. Effect of treatment regimen on QoL will also be investigated.

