### **Completion of Quality of Life Instruments**

Upon confirmation of eligibility and subsequent to inform consent, but preferably prior to randomization, the patient will be asked to complete the QoL questionnaires. It is preferable for the patient to complete the QoL questionnaires prior to randomization, though this is not mandatory. During the first two years of follow-up, the patient will be asked to complete the QoL questionnaires at 3, 6, 12, 18, and 24 months after randomization.

Quality of Life questionnaires are to be completed by the patient. They can be either mailed to the patient or completed by the patient at a clinic visit. The research nurse or delegated personnel at the clinical centre should indicate to the patient that the information the patient is providing is completely confidential. Instructions for the completion of questionnaires:

1. It is completed totally by the patient. Assistance should not be provided from the clinic staff or the patient's relatives unless the patient is blind or illiterate.
2. Only one answer to every question should be checked.
3. Clinical centre personnel should not review the questionnaire with the patient prior to completion.
4. Following completion, the research nurse or delegate must confirm verbally with the patient that the questionnaire has been fully completed. The patient should not change any responses after questionnaire completion.

[figure not shown]

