## APPENDIX V: HEALTH UTILITY INSTRUMENT

### Completion of Health Utility Instrument

Upon confirmation of eligibility and subsequent to inform consent, but preferably prior to randomization, the patient will be asked to complete the EQ-5D health utility questionnaire. It is preferable for the patient to complete the EQ-5D questionnaire prior to randomization, though this is not mandatory. During the first two years of follow-up, the patient will be asked to complete the EQ-5D questionnaire at 3, 6, 12, 18, and 24 months after randomization.

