## APPENDIX IX: ECONOMIC ANALYSIS

### Economic Evaluation

#### Costs

We have recently worked with Decision Support Services at Hamilton Health Sciences to successfully obtain costs for treatments, tests, medications, hospitalizations from the Ontario Case Costing Data Base for two of OCOG's other PET trials in lung cancer and breast cancer. We will use the same approach for this trial for costs related to hospitalizations, tests, procedures, medications and the use of other healthcare services. Costs related to physician services will be taken from the recent OHIP payment schedule. For chemotherapy costs we will employ a bottom up costing approach. For radiotherapy costs, we will review funding relationships between individual cancer centres, CCO and the MOHLTC to determine appropriate costs. For example, currently the MOHLTC reimburses cancer centres \$3500 per new patient radiated.

Total healthcare cost including all imaging and treatment will be calculated for each patient and averaged across patients in each study arm. Once patients develop recurrence of their cancer, treatments will vary. We will capture what treatments were received and obtain costs estimates for these but further data collection will not take place.

In addition to the two cancer specific QoL questionnaires, utilities will be estimated using the EQ-5D measurement system. The EQ-5D is a reliable and valid questionnaire designed to estimate societal valuations of the quality of life of patients (utilities). For this analysis, the UK tariff for estimation of utilities will be adopted. The EQ5D will be used to estimate utility values at each assessment point. These will then be aggregated using area under the curve methodology controlling for baseline utility value to allow estimation of quality adjusted life years (QALYs).

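### Baseline QLQ-C30, QLQ-CX24 and EQ-5D forms may be completed after randomization, by patients who know their allocation, yet still serve as baseline in the secondary QoL and QALY analyses

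*Protocol*

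**What the plan says.** Three places in the protocol set the timing of the baseline patient-reported forms, and they agree. Section 5 (Pre-treatment Evaluation), on all the questionnaires: "It is preferable for the patient to complete these questionnaires prior to randomization, although this is not mandatory". Appendix IV, on the QLQ-C30 and QLQ-CX24: "It is preferable for the patient to complete the QoL questionnaires prior to randomization, though this is not mandatory". Appendix V, on the EQ-5D: "It is preferable for the patient to complete the EQ-5D questionnaire prior to randomization, though this is not mandatory". Informed consent is the only firm lower bound, and no firm upper bound is written.

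The baseline score then has three uses:

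- Section 13.4, as the reference for descriptive changes: "The mean and standard deviation of each QoL domain will be calculated at each time point, along with changes from baseline".
- Appendix IX, where utilities are "aggregated using area under the curve methodology controlling for baseline utility value" to give QALYs.
- Section 13.3, as a condition of entry: "All patients who complete the baseline QoL and at least one follow-up QoL questionnaire will be included in the QoL Analysis set". The same set serves the economic outcomes. Nothing there depends on when the baseline form was completed.

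**The concern.** A baseline value protects a randomized comparison because allocation cannot have affected it. Section 6.2 allocates patients to PET-CT or no PET-CT, and no sham or blinding is described. That the trial is open-label is an inference, but no other reading fits. A patient who completes her form after randomization may answer in the knowledge that she will, or will not, have the extra scan.

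The instruments can register such a reaction. The EQ-5D asks about health on the day and has an anxiety/depression dimension. Most QLQ-C30 items look back one week and include tension, worry and depressed mood.

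If late answers differ by arm, subtracting them or adjusting for them moves part of an allocation effect into the baseline, or creates a difference where none exists. Entry to the QoL Analysis set could also rest on a form completed after allocation. Quality of life and economics are secondary objective 4, and Section 15 says the results are meant to inform policy makers. This is a data-collection rule: no later analysis can recover a pre-randomization answer that was never collected.

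**Working it through.** **The plan's own figure.** The only design calculation is the primary sample size in Section 13.2: 25% versus 45%, 2:1 allocation, two-sided α = 0.05, 90% power. With a continuity correction this gives 96 controls, so 96 + 192 = 288, as stated. Exact Fisher power at 96/192 is 0.915. The point here neither disputes nor depends on that figure.

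**The timing rules side by side.** Section 5 requires the chest imaging and the creatinine and blood sugar tests within 28 days before randomization. The patient-reported forms in the same section have no such limit. Section 7 puts the imaging within 4-6 weeks after randomization. Follow-up forms are due at 3, 6, 12, 18 and 24 months from randomization. Read literally, a form completed days or weeks after allocation still counts as baseline.

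**What a late form does.** The protocol supplies none of the following, so all three are assumptions:

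- f = share of PET-CT-arm baselines completed late;
- d = shift in those answers relative to the control arm, in standard deviations;
- ρ = correlation between baseline and follow-up, with equal standard deviations.

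With no true effect, the bias in the change-score contrast is f × d, and in the baseline-adjusted contrast about ρ × f × d.

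| f | change score | adjusted, ρ = 0.4 | ρ = 0.6 | ρ = 0.8 |
|---|---|---|---|---|
| 10% | 0.10d | 0.04d | 0.06d | 0.08d |
| 25% | 0.25d | 0.10d | 0.15d | 0.20d |
| 50% | 0.50d | 0.20d | 0.30d | 0.40d |
| 100% | 1.00d | 0.40d | 0.60d | 0.80d |

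A simulation with f = 0.5, d = 0.3 and ρ = 0.6 gave spurious differences of 0.150 SD (formula: 0.5 × 0.3 = 0.150) and 0.088 SD (formula: 0.6 × 0.150 = 0.090). This confirms the mechanism. It does not estimate the bias in this trial.

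**QALYs.** Under the trapezoidal rule over 0, 3, 6, 12, 18 and 24 months, the baseline EQ-5D carries 0.25/2 = 0.125 of 2.0 years, or 6.25%. If the late score is also the first point of the curve, it enters the outcome as well as the covariate.

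**The scan-result route.** Section 13.2 postulates palliative treatment in 20% of the PET-CT arm and 10% of the CT arm. Suppose a share f of forms in both arms came after the result, and each patient told that treatment is palliative scored lower by u. The mean difference between arms would be f × (0.20 − 0.10) × u = 0.10 × f × u. At f = 25% that is 0.025u; even at f = 100% it is 0.10u.

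**The case against.** The strongest reply is that the schedule already points to early completion. Appendices IV and V ask for the forms once eligibility is confirmed and consent given, and eligibility must be confirmed before randomization. Appendix III lists them under Screening Baseline, ahead of the intervention column, and Section 5 concerns pre-treatment evaluation. The rule states the right preference, is consistent across three places, and looks like a deliberate choice in favour of completeness. All of that stands, and it makes very late forms unlikely. It does not cancel a permission written three times.

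A reader might go further in three ways that the document does not support.

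- That baselines will be contaminated by scan results, with twice the proportion of PET-CT patients told their treatment is palliative. This needs forms completed after imaging has been reported, which runs against the order in Appendix III. It is possible only because no cut-off is written, and it is the weaker route.
- That the QALY bias can be quantified. Any figure would be an assumed shift multiplied by an assumed slope, with no input from the protocol.
- That the repeated-measures model in Section 13.4 is faulty because it names no baseline covariate. That is ordinary SAP content. Section 13.4 mentions changes from baseline only in its descriptive sentence and does not say that the model's outcome is a change score.

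It can also be objected that simply calling late forms missing would do harm. Under Section 13.3 those patients would then leave the QoL Analysis set, and with it both the QoL and the economic analyses. That objection is right, and the fix has to deal with it.

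**Conclusion.** The point holds as an avoidable weakness in data collection, not as a contradiction in the protocol. Followed as written, the rule lets a value that allocation may have affected act as reference, covariate and entry condition. The conclusion rests on two things: that patients know their allocation, which is inferred from the absence of any blinding, and that some will use the permission.

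The size cannot be derived from the document. It scales with the share of late forms and the between-arm shift in their answers, and is zero if no form is late. The contaminated score enters only the secondary QoL and cost-utility analyses. Treatment delivered, EFS, OS and sample size are untouched. The cost-effectiveness ratio based on treatment delivered does not use baseline utility, although Section 13.3 runs it in the same analysis set. The case for acting is that prevention is cheap and later repair is not possible.

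**What to change.** 1. In Section 5, Appendix IV, Appendix V and Appendix III, require the QLQ-C30, QLQ-CX24 and EQ-5D after consent and before randomization. Make this a checklist item in the web randomization system (IRIS).
2. Record the completion date of every baseline form. The QLQ-C30 form in Appendix IV already asks for the date; make sure that it is captured for the EQ-5D too.
3. State that a form completed after randomization is not used as the baseline reference or covariate in the main QoL and QALY analyses.
4. Amend Section 13.3 so that patients with a late form stay in the QoL Analysis set with baseline treated as missing. Section 13.1 already assumes that missing economic data are missing at random; the handling method can go in the SAP.
5. Add a sensitivity analysis that uses the late forms as baseline.

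Cost: wording in five places and one checklist step. Consent already precedes randomization, so no visit is added. Some baselines will be missing where a patient still completes the form late. The sample size stays at 288 and the power for the primary outcome at about 91.5%.
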